## 1 6. Methods, criteria, and interpretation for safety evaluation including adverse reactions

### 16.1 Evaluation methods

Adverse Event (AE) refers to any harmful and unintended sign (including abnormal laboratory results), symptom, or disease that occurs in a study participant who has been administered the herbal preparation, regardless of a causal relationship with the herbal preparation.

Adverse Drug Reaction (ADR) refers to any harmful and unintended reaction at any dose of the herbal preparation, where a causal relationship with the herbal preparation cannot be ruled out. In this study, all adverse events except those assessed as "unrelated" will be classified as ADRs.

The Case Report Form will document the symptoms and signs of adverse reactions, their duration (start and end dates), severity, causal relationship with the herbal preparation, actions taken regarding the adverse reaction, and outcomes comprehensively.

The safety evaluation will include:

- Adverse events, vital signs, laboratory tests, heart rate variability tests

### 16.2 Evaluation criteria

#### (1) Severity of adverse events

The severity of adverse events (Intensity) will be evaluated as follows:

| severity | explanation                                                                                                                                 |
|----------|---------------------------------------------------------------------------------------------------------------------------------------------|
| Mild     | Minimal interference with normal daily activities (function) and requires no special treatment.                                             |
| Moderate | Causes discomfort and interferes with normal daily activities (function). The participant can continue the trial but may require treatment. |
| Severe   | Causes significant discomfort, making normal daily activities (function) impossible, requiring treatment or hospitalization.                |

#### (2) Causal relationship with the administered herbal medicine preparations

The relationship with the herbal preparation will be classified by the investigator according to the criteria in Annex 77 of the Rules on Safety of Drugs and Medical Devices, and the investigator's opinion will also be recorded.

| Causal Relationship   | Judgement Criteria                                                                                                                                                                                                                                                                                                                                                                                                                                              |
|-----------------------|-----------------------------------------------------------------------------------------------------------------------------------------------------------------------------------------------------------------------------------------------------------------------------------------------------------------------------------------------------------------------------------------------------------------------------------------------------------------|
| Clear Relationship    | 
 
• Evidence of administration of the drug and a plausible temporal sequence of adverse event onset.
 
• The adverse event is more likely explained by drug administration than by any other cause.
 
• The adverse event disappears upon discontinuation of the drug.
 
• Positive re-challenge (if feasible).
 
• Consistency with known information about the drug or its class.
 
 |
| Probable Relationship | 
 
• Evidence of administration of the drug and a plausible temporal sequence of adverse event onset.
 
• The adverse event is more likely explained by drug administration than by any other cause.
 
• The adverse event disappears upon discontinuation of the drug.
 
                                                                                                                            |
| Possible Relationship | 
 
• Evidence of administration of the drug and a plausible temporal sequence of adverse event onset.
 
• The drug administration is as likely as other causes to explain the adverse event.
 
• The adverse event disappears upon discontinuation of the drug (if conducted).
 
                                                                                                                     |
| Unlikely Relationship | 
 
• Evidence of administration of the drug, but other causes are more likely to explain the adverse event.
 
• The adverse event does not disappear upon discontinuation of the drug (if conducted) or results are ambiguous.
 
                                                                                                                                                                            |
| No Relationship       | 
 
• The participant did not receive the drug, or the temporal sequence of drug administration and adverse event onset is not plausible.
 
• There is a clear alternative cause for the adverse event.
 
                                                                                                                                                                                                    |
| Not Assessable        | 
 
• Incomplete information prevents assessing the relationship with the drug.
 
                                                                                                                                                                                                                                                                                                                                   |

## (3) Actions taken in response to adverse events

The actions taken in response to the adverse event will be categorized as follows:

- Drug withdrawn
- Dose reduced

- Dose not changed
- Unknown
- Not applicable

(4) Outcomes of adverse events

The outcomes of adverse events that occur during the study will be classified as:

- Recovered/Resolved
- Recovering/Resolving
- Not recovered/Not resolved
- Recovered with Sequelae/Resolved with Sequelae
- Death
- Unknown

(5) Predictable adverse reactions to the investigational drug

- Skin: Rash, urticaria, eczema, dermatitis exacerbation.
- Gastrointestinal: Loss of appetite, gastric discomfort, nausea, vomiting, diarrhea.

(6) Identification of major adverse reaction symptoms

- Skin: subjective sensations, physical examination
- Gastrointestinal: subjective sensations

### 16.3 Reporting adverse events

The principal investigator will educate the study personnel and participants or their guardians about all potential adverse reactions that may occur after the administration of the investigational drug and instruct them to report any occurrences.

The Case Report Form will document and retain records of all symptoms, their duration, severity, treatment, medication, progress, and causal relationship as per clinical trial management standards.

#### 16.3.1 Serious adverse events(SAE) and Serious adverse drug reactions(SADR)

SAEs and SADRs refer to adverse events or drug reactions occurring at any dose of the herbal preparation that result in:

- ① Death or life-threatening condition.
- ② Necessity for hospitalization or extension of hospitalization.

- ③ Permanent or significant disability or functional impairment.
- ④ Congenital anomalies or birth defects.
- ⑤ Medically significant conditions such as drug dependence, abuse, or blood disorders.

Any other condition that significantly impacts the participant's well-being or health, in the investigator's and related experts' medical judgment, will be considered a serious adverse reaction and appropriate actions will be taken.

The principal investigator will report all newly occurring serious adverse events during the clinical trial to the IRB following the institution's regulations. Continuous monitoring and additional reporting to the clinical trial support organization and IRB will be conducted. The principal investigator will notify the clinical trial sponsor, the Korea Institute of Oriental Medicine, and the monitoring personnel immediately to ensure appropriate actions are taken. When reporting a death, the principal investigator must submit additional information such as an autopsy report (if performed) and final medical records to the clinical trial support organization and the review board.

The following are not considered serious adverse events for "hospitalization or extended hospitalization":

- Diagnosis purposes
- Cosmetic surgery
- Precautionary examination
- Minor admissions (e.g., elective admission for social reasons)
- Long-term care or rehabilitation
- Relocation to a facility due to inability to continue home care
- Efficacy and safety assessments related to the study
- Scheduled treatment of the disease under study
- Pre-planned admissions without patient condition deterioration

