##### **1) Principal investigator responsibilities**

The principal investigator must immediately report any serious adverse event to the clinical trial

support organization or monitoring personnel within 24 hours of recognition and report to the IRB according to its regulations. Detailed follow-up reports must be provided within the same timeframe. Unexpected serious ADRs must be promptly reported to the clinical trial support organization and the IRB. Additional information, such as autopsy reports (if applicable) and final medical records, must be submitted when reporting deaths.

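### Section 16.3.1 exempts admissions for diagnosis or precautionary examination from the hospitalization criterion without requiring that they be unrelated to an adverse event

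*Protocol*

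**What the plan says.** Section 16.3.1 of the protocol gives five criteria that make an adverse event serious. The second is "Necessity for hospitalization or extension of hospitalization". A judgement clause follows: any other condition with a significant effect on the participant's health is also to be treated as serious, in the medical judgement of the investigator and related experts.

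The same section then lists nine kinds of admission, introduced by "The following are not considered serious adverse events for" and confined by the words that follow to hospitalization or its extension. The list includes "Diagnosis purposes", "Precautionary examination" and "Efficacy and safety assessments related to the study". Only the last item, "Pre-planned admissions without patient condition deterioration", refers to the participant's condition.

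Several duties depend on seriousness. Section 19, item 1, states: "The principal investigator must immediately report any serious adverse event", with a limit of 24 hours from recognition. Section 16.3.1 requires immediate notice to the sponsor and monitor, and an IRB report under the institution's rules. Section 14.4.1 tabulates SAEs and SADRs by group with incidence and 95% confidence intervals.

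**The concern.** The exemptions sit directly under the criterion that they narrow, and two of them describe what commonly happens after a new event: the participant is admitted so that the cause can be found, or as a precaution. If a site applies these items as written, an admission that meets criterion 2 is taken out again a few lines later.

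Whether an event is serious would then depend on how the admission is labelled. Two hospitals recruit for this trial, and the same admission could be classed differently at each. What is at stake is the expedited reporting route and the accuracy of the SAE and SADR counts. In a trial of 50 per arm those counts are likely to be small, so single classifications matter.

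**Working it through.** The protocol states no figure on this point that could be reproduced. The check sets the provisions side by side.

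**1. Which exemptions can cover an event-prompted admission.**
- Cosmetic surgery, social admission and relocation of care are, in their ordinary sense, not prompted by a new adverse event. Scheduled treatment is limited by being scheduled. The pre-planned item has its own limit.
- "Diagnosis purposes" and "Precautionary examination" have no limit of any kind. An admission to investigate a new symptom or laboratory abnormality fits their plain words.
- "Efficacy and safety assessments related to the study" is a weaker case. It most naturally means protocol assessments, but it does not say scheduled ones. Section 11.4.1.7 provides unscheduled visits because of adverse reactions and asks for the Visit 4 tests as far as possible. Section 11.4.1.4 places the ECG, AST, ALT, BUN and creatinine among those tests. In this protocol a study assessment can therefore itself be triggered by an event.

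**2. What the list leaves untouched.** It narrows criterion 2 only. Death or a life-threatening condition, disability, congenital anomaly, medically significant conditions and the judgement clause still apply. The gap is therefore confined to events whose only ground for seriousness is hospitalization.

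**3. What such an event would miss.**
- The 24-hour report (section 19, item 1).
- The immediate notice to sponsor and monitor, and the IRB report for SAEs (section 16.3.1).
- Its place in the SAE count and, if related, the SADR count (section 14.4.1).
- If it is also an unexpected drug reaction, SUSAR handling (section 16.3.2) and the 15-day report (section 19, item 4). The 7-day report is not affected, because fatal and life-threatening events are serious under criterion 1.
- Suspension for serious drug reactions (sections 19 and 20.7), which also depends on the classification.

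**4. Whether the unexpected-reaction branch is realistic.** Section 27 names liver dysfunction and interstitial pneumonia as rare risks. The product precautions (section 12.2) and the predictable reactions in section 16.2, item 5, list only skin and gastrointestinal effects. Section 16.3.2 judges expectedness against available drug information such as the package insert, which is not among the documents. If the insert matches section 12.2, a liver or lung reaction would be unexpected, and seriousness would be the remaining gate to SUSAR reporting.

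**5. What such an event would keep.** It remains an adverse event, and a drug reaction unless assessed as unrelated (section 16.1). It is recorded with severity and causality (sections 16.1 and 16.3) and followed (sections 11.4.2.26 and 19). Adverse reactions are regularly reported to the support institution (section 21.2), and adverse events and drug reactions are tabulated by group (section 14.4.1).

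**6. Size per participant.** Section 7, item 3, plans 50 per arm. If all 50 are in the Safety Set, one participant moved from serious to non-serious, with no other SAE, changes that arm's SAE incidence by 1/50 = 0.02, or 2 percentage points.

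**The case against.** The strongest case on the other side is that the list has a natural, harmless reading. Criterion 2 covers adverse events that lead to a need for hospitalization. Most of the list concerns admissions that no adverse event caused, such as cosmetic surgery or social reasons, and the diagnosis and precaution items can be read in that company. Severity is still captured too: section 16.2 grades as severe an event that makes normal daily activities impossible and requires treatment or hospitalization.

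The harmless reading is probably what the drafters meant, but the text does not say so. By limiting one item to participants who have not deteriorated, the list invites a site to read the others as unlimited. If the harmless reading is the intended one, the clause proposed below changes nothing except to state it.

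A reader might infer more than the documents support:
- **That every admission for work-up falls outside the SAE definition.** It does not. The other criteria and the judgement clause can still make the event serious, and because the list is confined to the hospitalization criterion it does not override them. New jaundice or interstitial pneumonia could qualify by those routes, depending on severity.
- **That nobody is told of the event.** The recording, follow-up, regular reporting and tabulation in step 5 contradict this. What is lost is speed and the serious label.
- **That all such events miss regulatory reporting.** The 15-day rule covers only drug reactions that are both serious and unexpected.
- **That a given share of hospitalized events would be hidden.** The protocol gives no expected number of admissions, so any such share would only restate an assumption.

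**Conclusion.** The point holds as a defect of definition. Two unqualified exemptions in section 16.3.1 conflict with criterion 2 of the same section and can produce a wrong classification when followed literally. The affected class is narrow: admissions to investigate a new or worsening event, or to observe it as a precaution, where hospitalization is the only ground for seriousness. For those, expedited reporting and the SAE and SADR counts can fail, while the adverse event record does not.

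The size is 2 percentage points of SAE incidence per reclassified participant in an arm of 50, which would be true of any single event in an arm of that size. How often it would occur cannot be derived from the documents. The conclusion assumes that a site applies the list by its plain words. The SUSAR consequence also assumes that the reaction is absent from the package insert.

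This should be corrected in the protocol, since the SAE definition and the reporting duties are fixed there.

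**What to change.** Reconcile the list in section 16.3.1 with criterion 2 by adding one clause that governs all nine items: the exemptions apply only when the admission was not prompted by a new or worsening sign, symptom or laboratory abnormality. In addition, limit the study-assessment item to assessments scheduled by the protocol.

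The study-assessment item need not be deleted, and exemptions need not be restricted to admissions planned before consent or made for non-medical reasons. Either change would turn protocol assessments or scheduled treatment arranged after consent into reportable admissions, although no adverse event is involved.

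The cost is one sentence, one qualifier and a note in site SAE training. The downside is a few more SAE forms.

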### **16.3.2 Unexpected adverse drug reactions**

Unexpected ADRs differ in nature or severity from the available drug information (e.g., package insert).

When "Suspected Unexpected Serious Adverse Drug Reactions (SUSAR)" occur, the IRB will be notified to decide whether to continue or suspend the trial, and the clinical trial support organization will report to the Ministry of Food and Drug Safety within the specified period.

The principal investigator will conduct the study in accordance with the Declaration of Helsinki.

#### **16.4 Follow-up of adverse events**

The principal investigator will follow up on all serious adverse events until resolution, stabilization, or loss to follow-up. In cases of significant changes, such as discharge from hospitalization, a follow-up report will be documented and submitted to the clinical trial support organization via email or fax.

#### **17. Compensation regulations for subjects**

If physical injury (including death) occurs to the study participant due to the research, the clinical trial support organization is legally responsible for compensation in accordance with compensation regulations. Compensation will also be provided for injuries occurring during corrective treatments related to adverse reactions.

#### **18. Informed consent of participants**

The researcher must explain all aspects of the study, including the effects, adverse reactions, and safety of the investigational drug, to the participant and obtain voluntary signed consent before proceeding with the study.

#### **19. Actions in case of adverse events**

Participants will receive necessary examinations and treatment immediately from the researcher in case of adverse events. The study will be immediately suspended in case of serious ADRs, and appropriate actions will be taken according to the principles for responding to adverse events.

Participants with adverse events will be continuously monitored via phone or outpatient visits until resolution or stabilization, or until follow-up is no longer possible. The duration of monitoring will be documented in the case report form.

During the clinical trial, responsibilities in the event of a "serious adverse event" are as follows:

##### **1) Principal investigator responsibilities**

The principal investigator must immediately report any serious adverse event to the clinical trial

support organization or monitoring personnel within 24 hours of recognition and report to the IRB according to its regulations. Detailed follow-up reports must be provided within the same timeframe. Unexpected serious ADRs must be promptly reported to the clinical trial support organization and the IRB. Additional information, such as autopsy reports (if applicable) and final medical records, must be submitted when reporting deaths.

## 2) Study Personnel Responsibilities

Study personnel must immediately report any serious adverse event to the principal investigator and the clinical trial support organization.

## 3) IRB responsibilities

The IRB must take necessary actions, such as ordering the suspension of all or part of the study, if unexpected serious ADRs or new information that may negatively affect the participant's safety or the study's conduct arises.

## 4) Clinical trial support organization responsibilities

The clinical trial support organization must report all serious and unexpected ADRs to other relevant researchers, the Ministry of Food and Drug Safety, and, if necessary, the IRB within 15 days. If the event results in death or is life-threatening, reporting must occur within 7 days, with detailed information provided within 8 days of the initial report. When reporting unexpected serious ADRs to the Ministry of Food and Drug Safety, the clinical trial support organization must include the ADR report and a summary in the CIOMS- I format. Any additional information must be reported periodically until the adverse reaction is resolved or follow-up is no longer possible. Researchers must actively cooperate in providing data and information for these reports.

## **20. Measures for protecting the safety of research subjects**

### **20.1 Clinical trial institution**

The head of the institution must ensure that each clinical trial phase is equipped with the necessary facilities and professional staff, thoroughly preparing to conduct the trial properly.

### **20.2 Principal investigator**

The principal investigator must secure the necessary personnel, equipment, and facilities to conduct the research appropriately and safely throughout the study period.

### **20.3 Research staff**

Research staff must fully understand the research protocol, information about the herbal preparations used in the study, and their duties and responsibilities related to the research.

### **20.4 Approval and modification of the research protocol**

When seeking approval for the research protocol or making changes to an approved study, the protocol or amended protocol must be approved by the Institutional Review Board (IRB) for each stage of the study.

### **20.5 Familiarity with the research protocol**

This clinical trial is prepared with the rights and welfare of the subjects in mind, based on the Declaration of Helsinki. Investigators and staff must thoroughly analyze and understand the protocol and proactively address any issues related to the subjects.

### **20.6 Accurate selection of research subjects**

Prior to the clinical trial, a thorough evaluation is conducted to assess the suitability of subjects through sufficient interviews and examinations.

